#### Blinding

Due to the nature of the interventions, it is not possible to blind study participants or research nurses and interviewers after assignment to a study arm. This is because, as part of the study procedures research, nurses must observe participants swallow their pills via VDOT, and at follow-up visits, interviewers must collect participant data regarding medication adherence. The research staff allocating participants to study groups during randomization will be blinded to the sequence. This is to minimize the likelihood that the research staff will be able to predict the next study arm assignment. Study investigators will be blinded to the allocation and any preliminary analyses before the end of the study. Only the trial statistician will be unblinded to the analyses. The data collection tools used for this purpose include information about how pill-swallowing is conducted (UC-DOT or VDOT), thus making the study group assignment obvious.

#### Description of Standard Procedures

The trial and intervention are described according to the SPIRIT (Standard Protocol Items: Recommendations for Interventional Trials) guidelines [32]. Regardless of the assigned study group, all participants will attend an initial face-to-face educational session, which will provide information on (1) the importance of medication adherence according to the daily TB drug regimen; (2) the correct way to take TB pills, including dose, timing, and the importance of taking pills whole; (3) storage of pills and what to do in the event of a missed dose; and (4) the importance of reporting (in-person or through the VDOT app) any problems related to TB medications, such as side effects, adverse events, symptoms, lost pills, lost or malfunctioning smartphone or app, etc, as well as any study-related issues.

#### Control: Usual-Care Directly Observed Therapy (UC-DOT)

Participants will receive UC- DOT as administered in routine clinical practice under the Uganda National TB program. Routine DOT typically involves treatment observation 3-5 times per week by a designated treatment supporter who could be a trained community worker, a volunteer lay-worker, a family member, a friend, or community linkage facilitator, with the weekend doses self-administered. The name and phone contact details of each designated treatment supporter for each patient are documented. The treatment observation and support occur at any location mutually agreed upon between the patient and their treatment supporter. To document adherence, the patient records daily doses taken on a predesigned treatment card issued at the clinic and returns it at every routine visit. Adherence is further assessed using patient self-reports, pill counts, and clinic attendance for prescription refills. Study research assistants will work in partnership with designated treatment supporters to collect study information on adherence from clinic records coupled with a structured adherence questionnaire at follow-up visits. Patients in the UC-DOT control group will be followed up for missed doses and routine visits according to the National TB program guidelines. Research staff will only follow up with participants for scheduled study visits and procedures.

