#### Intervention: Asynchronous Video Directly Observed Therapy (VDOT)

Upon assignment to the intervention study group, participants will receive detailed training (in English or Luganda) on the VDOT app using a training manual provided by the VDOT software developer. The asynchronous VDOT intervention comprises a smartphone with a SIM card, the preloaded VDOT app, a free weekly internet data subscription of 350 MBs paid for by the study at commercial rates, and daily SMS text message medication reminders. The VDOT app is a free downloadable app through the App Store, and the system is Health Insurance Portability and Accountability Act (HIPAA)-compliant and has been validated [33]. Additionally, patients will receive a weekly incentive in the form of social bundles or airtime minutes each time they successfully submit videos for 7 consecutive days. The smartphone will have a unique phone number to ensure that SMS reminders and other phone communications are sent specifically to study participants. The VDOT app is free and downloadable from the Play Store. A unique personal identification number (PIN) will be assigned to each person at registration in the VDOT system to facilitate login into the VDOT app. The PIN will be a security feature that will prevent nonstudy participants, such as other family members or friends, from accessing the app. The app is equipped with video recording features that allow patients to record videos of themselves swallowing pills 7 days each week (Figure 2). To ensure safety and to address concerns that side effects may be missed with limited face-to-face contact, patients are also encouraged to report any adverse events on the daily videos. After the recording ends, an automatic, encrypted, time-stamped video is transferred through a cellular connection and uploaded to a secure cloud server for storage and playback. This enables patients to securely and confidentially record and submit daily medication doses. Once a submission is completed, the patient cannot retrieve or access the video. The smartphone will automatically receive the internet bundles to facilitate video submission.

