### Study Outcomes

The primary outcome measure is the level of adherence calculated as the fraction (proportion) of expected doses observed (FEDO) over the 6 months of treatment or by the end of the study following randomization. Since direct observation as a way of measuring medication adherence may be challenging to employ consistently in the UC-DOT group, we will also use self-reports and pill counts as indirect measures of adherence and then triangulate the results. Time-to-treatment completion will be assessed as the main secondary outcome. Other outcomes will be sputum smear conversion at 2 and 6 months or the end of treatment, clinical response as a measure of self-reported improvement in TB symptoms, and weight gain at 2, 4, and 6 months or the end of treatment. Other outcomes will be self-reported side effects, the occurrence of adverse events, and patient satisfaction at the exit of the study. Patient satisfaction will be evaluated in 2 ways: (1) overall satisfaction with VDOT or UC-DOT, and (2) satisfaction with specific areas, such as the VDOT technology and app use; information and training received; interaction with treatment supporters, health providers, or research staff; and privacy and confidentiality during medication intake. Additionally, at study exit, we will conduct individual qualitative interviews for both UC-DOT and VDOT participants to capture detailed information about participant experiences during the study.

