### Statistical Analyses

Intention-to-treat analysis will be conducted where all patients will be analyzed according to the arm to which they were originally randomized. VDOT treatment observations will be classified as completed if ingestion of all medicines is observed, or if videos are received but not viewable because of a technical complication (given that patients would have no control over whether videos were corrupted). The sensitivity analysis will consider only videos for which all medications are observed as completed. An adherence proportion will be observed for each individual in this study. Let p_ij_ be the adherence proportion for individual j (j=1, ..., n) in treatment group i (i=0 for VDOT and i=1 for UC-DOT). Then, let p_0_ and p_1_ equal to the average FEDO in the VDOT and UC-DOT arms, respectively. Similarly, let s_0_=s.e.( p_0_) be the standard error of p_0,_ and similarly, let s_1_ be the standard error of p_1_. The standard *t* test statistic will be used to calculate a *P* value based on the following statistic:

The Welch *t* test will be used to calculate significance. However, since we do not have estimates of s_0_ and s_1_, this formula is not useful for power calculation. Therefore, to calculate power and sample size, we treat the response for each individual as binary (0 or 1), indicating adherence or nonadherence. This corresponds to using an adherence cutoff value of FEDO with equal-to or greater than 80% as a threshold for adherence. This binary response variable for adherence will be used in the final analysis to facilitate comparison with previous clinical trials [15].

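### The primary outcome, the fraction of expected doses observed (FEDO), is not measured alike in the two arms, and on its plain reading it conflicts with the control rate used for the sample size

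*Protocol article*

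**What the plan says.** All references are to the Protocol article.

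- **Outcome.** Study Outcomes makes the primary measure "the level of adherence calculated as the fraction (proportion) of expected doses observed (FEDO) over the 6 months of treatment". The sentence then offers study end, after randomization, as an alternative limit.
- **Regimen.** Description of Standard Procedures describes a daily drug regimen.
- **Control arm.** Under Control: Usual-Care Directly Observed Therapy, "Routine DOT typically involves treatment observation 3-5 times per week by a designated treatment supporter", and on Saturdays and Sundays the patient is not watched ("with the weekend doses self-administered"). The supporter may be a relative or friend. The same section adds: "To document adherence, the patient records daily doses taken on a predesigned treatment card issued at the clinic". It also lists self-report, pill counts and refill attendance.
- **Intervention arm.** The VDOT app lets patients "record videos of themselves swallowing pills 7 days each week". When recording or upload is not possible, the nurse uses self-report, pill counts and refills. Potential Limitations likewise fills gaps in the records from self-report.
- **Combining sources.** Study Outcomes acknowledges that direct observation is hard to apply consistently in usual care, and says "we will also use self-reports and pill counts as indirect measures of adherence and then triangulate the results".
- **Analysis.** Statistical Analyses compares mean FEDO by a Welch t test, and adds a binary response "using an adherence cutoff value of FEDO with equal-to or greater than 80% as a threshold for adherence", which is also used for power and in the logistic models. Received but unviewable videos count as completed in the main analysis.
- **Planning rates.** Sample Size assumes 85% (VDOT) against 63% (usual care).

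**The concern.** FEDO has two parts, the doses expected and the doses observed, and the article fixes neither in a way that works for both arms. In VDOT every daily dose can be witnessed. In usual care, as the article describes it, between two and four of the seven weekly doses are not witnessed even when the patient takes all of them.

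A difference in FEDO can therefore arise from how often someone is watching. The stated objective is to improve medication adherence, so the trial could report an adherence benefit that is only a difference in observation. If the gap is filled from patient records, a real benefit could be hidden instead. The article leaves the choice between these routes open in an open-label trial whose interviewers know the arm (Blinding).

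**Working it through.** **1. The plan's own figure.** Inputs from Sample Size: 0.85 vs 0.63, two-sided 5%, 80% power, 1:1. With the pooled-variance formula and mean proportion 0.74:

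n per arm = [1.96·√(2·0.74·0.26) + 0.842·√(0.85·0.15 + 0.63·0.37)]² / 0.22² = 61.2, rounded up to 62, so 124 in total.

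Power at 62 per arm is 80.5%. The odds ratio is (0.63/0.37)/(0.85/0.15) = 0.30. Inflation gives 124/0.86 = 144.2, against 144 stated. The arithmetic reproduces and is not at fault.

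**2. Route A: all daily doses expected, only witnessed doses counted.** Highest possible control FEDO = observed days / 7:

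| Observed per week | Ceiling |
|---|---|
| 3 | 3/7 = 42.9% |
| 4 | 4/7 = 57.1% |
| 5 | 5/7 = 71.4% |

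Reaching 80% takes 0.8 × 7 = 5.6 witnessed doses a week. On the described schedule no control reaches it, whereas Sample Size plans for 63%.

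The analysis of means is affected too. If both arms truly take 90% of doses and every VDOT dose taken is filmed, mean FEDO is 90% in VDOT and 0.90 × 3/7 = 39% to 0.90 × 5/7 = 64% in control. That is a gap of 26 to 51 points with no difference in doses taken.

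For the binary analysis with 62 per arm and no control at 80%, four VDOT patients at 80% already give a chi-square P below .05. The chance of that is 88% if only 10% of VDOT patients reach the cutoff, and 99.9% if 20% do.

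**3. Route B: unwitnessed doses credited from card, self-report or pill count.** Suppose all witnessed doses are taken and a share c of the others is credited. Then 80% is reached when c = (5.6 − k)/(7 − k):

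- k = 3: 2.6/4 = 65%
- k = 5: 0.6/2 = 30%

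The cap disappears, but whether a control patient passes now depends largely on doses that the patient recorded, while a VDOT patient passes mainly on video.

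**4. Size under Route B (illustrative only).** Assumptions not in the article: control FEDO follows a Beta distribution with precision 3, 5 or 10 and 63% of patients truly at or above 80%; patient records add a uniform 5 or 10 points; VDOT stays at 85%.

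| Over-reporting | Recorded control share at ≥80% (precision 3 / 5 / 10) | Power at 62 per arm |
|---|---|---|
| none | 63% | 80.5% |
| 5 points | 70 / 72 / 75% | 53 / 43 / 26% |
| 10 points | 75 / 79 / 85% | 27 / 14 / 5% |

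These figures show the direction and how sensitive the result is. They do not predict this trial.

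**The case against.** The strongest reply is that the authors do not intend Route A. They acknowledge the difficulty in usual care, add indirect measures, describe a card that covers daily doses, qualify 3-5 times with *typically*, and plan for 63% of controls above the cutoff. All of this stands. A reader might infer that controls simply cannot reach 80%. The article does not support that, because the cap needs both a daily denominator and a witnessed-only numerator, and neither is stated.

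A reader might also infer that only usual care has indirect sources. That is not so: VDOT has its own fallback for days without video, and pill counts and the 10-item questionnaire are planned at follow-up visits without restriction by arm.

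Entry up to one month after treatment start, beside a six-month period, might suggest that late entrants are penalised. But Study Outcomes goes on to refer to the end of the study following randomization, and late entry can occur in either arm, so this is no evidence of unequal measurement.

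The over-reporting figures treat 63% as true adherence. If that rate came from routine records or self-report, over-reporting is already in it and the calculation counts it twice. The article does not say where the 63% comes from.

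Finally, a combination rule may sit in a full protocol or analysis plan not shown. The absence of that rule is therefore not the point. The point is that the plain definition of the outcome, the described control schedule, the 80% cutoff and the 63% planning rate, all stated here, do not fit together.

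**Conclusion.** The concern holds in conditional form. FEDO is not measured alike in the two arms.

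- **Literal count over daily doses.** A fully adherent control patient on the described schedule scores at most 43-71%. This contradicts the planned 63% at or above 80% and favours VDOT through the observation schedule alone, in both the mean and the binary analysis.
- **Crediting other sources.** Mainly patient-recorded doses are compared with mainly filmed doses, and the bias may run against VDOT.

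The direction of bias depends on a rule that the article does not give, and neither route isolates doses taken. The 43-71% rests only on the article's own schedule. The size of the bias in the second case cannot be fixed from the article. This should be settled before any comparative adherence data are seen.

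**What to change.** 1. Reconcile the control-arm, intervention-arm, Study Outcomes, Sample Size and Statistical Analyses sections. Give one definition of an expected dose and one of an observed dose, with one source hierarchy for both arms, counted from randomization.
2. State which definition the 63% and 85% planning rates refer to.
3. Beside FEDO, prespecify a comparison on the measures planned alike in both arms: pill count where available and the 10-item questionnaire at months 2, 4 and 6.
4. If FEDO remains primary on witnessed doses, word its conclusion as doses observed. Claim improved adherence only if the same-source comparison supports it.

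Limiting the denominator to weekday doses is not enough: a control patient observed three times a week would still be held to 3/5 = 60%.

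**Cost.** FEDO can stay primary and the data sources are already planned, so the change is mainly wording plus one added analysis. Enrollment has begun, so it needs a dated amendment, best made before the interim check of adherence at 50% enrollment. The downsides are that pill counts and questionnaires are less precise than video, pill counts are taken only when possible and may be incomplete, and the apparent advantage of VDOT may be smaller.

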#### Intervention: Asynchronous Video Directly Observed Therapy (VDOT)

Upon assignment to the intervention study group, participants will receive detailed training (in English or Luganda) on the VDOT app using a training manual provided by the VDOT software developer. The asynchronous VDOT intervention comprises a smartphone with a SIM card, the preloaded VDOT app, a free weekly internet data subscription of 350 MBs paid for by the study at commercial rates, and daily SMS text message medication reminders. The VDOT app is a free downloadable app through the App Store, and the system is Health Insurance Portability and Accountability Act (HIPAA)-compliant and has been validated [33]. Additionally, patients will receive a weekly incentive in the form of social bundles or airtime minutes each time they successfully submit videos for 7 consecutive days. The smartphone will have a unique phone number to ensure that SMS reminders and other phone communications are sent specifically to study participants. The VDOT app is free and downloadable from the Play Store. A unique personal identification number (PIN) will be assigned to each person at registration in the VDOT system to facilitate login into the VDOT app. The PIN will be a security feature that will prevent nonstudy participants, such as other family members or friends, from accessing the app. The app is equipped with video recording features that allow patients to record videos of themselves swallowing pills 7 days each week (Figure 2). To ensure safety and to address concerns that side effects may be missed with limited face-to-face contact, patients are also encouraged to report any adverse events on the daily videos. After the recording ends, an automatic, encrypted, time-stamped video is transferred through a cellular connection and uploaded to a secure cloud server for storage and playback. This enables patients to securely and confidentially record and submit daily medication doses. Once a submission is completed, the patient cannot retrieve or access the video. The smartphone will automatically receive the internet bundles to facilitate video submission.

The VDOT system has a feature to adapt the text messages either in English or Luganda (Figure 3). These text messages will include reminders to motivate patients to continue taking their medications. An example of these messages is “It’s time to take your pills and send a video. Taking your pills will help you get better.” A single SMS text will be sent to each participant in the morning as a reminder; a second text will be sent within 8 hours of the first if a video is not received by the system.

At the clinic, a trained study nurse will log into a secured, HIPAA-compliant VDOT system via a tablet or laptop to download and review patients’ daily videos and document medication adherence. On days when video recording or uploads are not possible, medication adherence will be assessed using patient self-reports, pill counts, and prescription refills at the clinic. The nurse will thus be able to track missed doses and reported side effects, and follow up with appropriate support or advice. Participants will sign an agreement to return the smartphone to the clinic upon completing their full course of treatment.

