#### Follow-up of Participants With Missed Videos or Study Visits

A predefined follow-up protocol will be used to contact study participants in cases of missed doses or videos. The research staff will make 2 phone call attempts within the first 24 hours of a missed, expected video to establish dosing history and the reason for missing videos. If there is no response from the participants within 72 hours, the research team will escalate the follow-up to a field visit to trace the participant at home or work. After a period of 2 weeks from when the intensive, active follow-up protocol has been completed, there will be a waiting interval of 2 weeks, hoping that the participant will call back or return to the clinic for a routine visit. If the participant does not show up for the scheduled clinic visit, the national TB program staff will get involved in support of the patient. A declaration of “lost to follow” will be made if the participant does not return for 2 consecutive months, in line with the standard World Health Organization’s guidelines [34].

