Study measurements will be done at baseline and follow-up at months 2, 4, and 6 to ensure close monitoring of all patients in treatment. All participants, regardless of the study group, will complete a questionnaire at these follow-up visits (Multimedia Appendix 2 and 3). The follow-up questionnaire will address issues such as (1) patients’ current use and any changes in experience with a cell phone, such as acquiring a personal cell phone or smartphone; (2) transportation and other costs to and from the TB clinic; (3) TB treatment experiences using VDOT or UC-DOT; (4) experiences when using a phone to record videos or when receiving support under the usual DOT; (5) satisfaction with TB and VDOT or UC-DOT; (6) ongoing support received during treatment; (7) side effects experienced; (8) difficulties with medication supply or transportation to the clinic; and (9) privacy, confidentiality, and stigma concerns. For internal validity, adherence will also be measured at follow-up visits by pill counts (when possible) and using a 10-item self-reported adherence questionnaire [36] (Multimedia Appendix 4).

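### Only the VDOT arm has a daily, nurse-reviewed route for reporting adverse events, so a between-arm comparison of all recorded events is open to detection bias

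*Protocol article*

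**What the plan says.** The Study Outcomes section names both items without restricting them to an arm: "Other outcomes will be self-reported side effects, the occurrence of adverse events, and patient satisfaction at the exit of the study". The section on collecting and reporting adverse events says that data on all such events are gathered from consent and enrolment until the study ends. It sets no common source or schedule for the two arms.

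For the VDOT arm, the intervention section says that "patients are also encouraged to report any adverse events on the daily videos". The app's recording features "allow patients to record videos of themselves swallowing pills 7 days each week". On the review of these videos it adds: "The nurse will thus be able to track missed doses and reported side effects, and follow up with appropriate support or advice". The section on missed videos gives this arm one more contact: "The research staff will make 2 phone call attempts within the first 24 hours of a missed, expected video".

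For the usual-care arm, the control section says: "Routine DOT typically involves treatment observation 3-5 times per week by a designated treatment supporter". The supporter may be a lay volunteer, relative or friend. Research assistants work with supporters to obtain adherence information; adverse events are not mentioned. The section ends: "Research staff will only follow up with participants for scheduled study visits and procedures".

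Two provisions are shared. The educational session under Description of Standard Procedures tells every participant to report side effects and adverse events, in person or through the app. Study Outcomes also says of months 2, 4 and 6: "All participants, regardless of the study group, will complete a questionnaire at these follow-up visits". Side effects experienced is one of its topics. The appendix list shows a separate follow-up questionnaire for each arm (Multimedia Appendices 2 and 3).

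**The concern.** The same event has a daily path into the study record in one arm. In the other, the only research contact described is at scheduled visits. Participants, nurses and interviewers all know the allocation. With equal true event rates, an arm with more opportunities to report will tend to show more recorded events, so a count of everything recorded mixes the effect of VDOT with the effect of asking more often.

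What is at stake is the safety comparison. VDOT could appear to cause more side effects when it only records more of them. Adverse events also go to the data monitoring committee and, in summary, to the funder, so the same imbalance would appear in any tabulation by arm made for them.

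**Working it through.** **1. Routes into the study record**

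| Route | VDOT | Usual-care DOT |
|---|---|---|
| Baseline instruction to report problems | yes | yes |
| Questionnaire at months 2, 4 and 6 covering side effects | yes | yes |
| Daily video, reporting encouraged, reviewed by a study nurse | yes | no |
| Research-staff call after a missed video | yes, to establish dosing history and the reason | no |
| Treatment supporter, typically 3-5 times a week | not part of the intervention | yes, but no route to the adverse event record is stated |

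The first two rows are balanced. The third is the real asymmetry. The fourth adds contact, but its stated purpose is not to elicit events. The fifth gives usual care frequent contact without a described link to the study's data.

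**2. Size, by assumption**

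The plan has no figure for adverse events to reproduce; its only design calculation concerns adherence. Let the true risk π be the same in both arms and let d be the share of patients with an event whose event is recorded. The recorded risk is π × d, so

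apparent risk ratio = (π × d_VDOT) / (π × d_UC) = d_VDOT / d_UC.

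Assume d_VDOT = 0.90:

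- d_UC = 0.90: 0.90/0.90 = 1.00
- d_UC = 0.80: 0.90/0.80 = 1.125, about 1.13
- d_UC = 0.70: 0.90/0.70 = 1.29
- d_UC = 0.50: 0.90/0.50 = 1.80

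**3. Chance of a spurious significant excess in VDOT**

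Inputs: n = 72 per arm (Sample Size section), two-sided 5% level, normal approximation. With Δ the difference in recorded risks, se0 the pooled and se1 the unpooled standard error, the chance is Φ((Δ − 1.96 × se0)/se1).

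Example with π = 0.30 and d_UC = 0.70:

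- Recorded risks are 0.30 × 0.90 = 0.27 and 0.30 × 0.70 = 0.21, so Δ = 0.06.
- se0 = √(2 × 0.24 × 0.76/72) = 0.0712.
- se1 = √((0.27 × 0.73 + 0.21 × 0.79)/72) = 0.0710.
- Φ((0.06 − 0.1395)/0.0710) = Φ(−1.12) = 13%.

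| True risk (assumed) | d_UC = 0.80 | d_UC = 0.70 | d_UC = 0.50 |
|---|---|---|---|
| 20% | 5% | 10% | 28% |
| 30% | 6% | 13% | 42% |
| 50% | 9% | 23% | 72% |

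With equal capture the chance in this direction is 2.5%. A modest capture gap does little; a wide one matters.

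**The case against.** Several points on the other side are sound.

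- No section says that events from all sources will be pooled, or that adverse events will be formally tested between arms. Statistical Analyses names adherence, sputum conversion and clinical response for the trend comparisons, not adverse events. A reader might infer a pooled test from the outcome list and the rule to collect all events, but the text does not state one. The point is therefore conditional.
- Both arms are taught to report problems and both are asked about side effects at months 2, 4 and 6. A comparison confined to those answers would be largely protected.
- Usual-care patients have frequent supporter contact, and the video prompt is there because VDOT reduces face-to-face contact. The control section does not say that they cannot report events. Equal capture is not shown, but neither is the size of any gap.
- The calls after missed videos should not be read as adverse event prompts.
- Choosing which source feeds a table is normally left to the analysis plan.

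The last point does not dispose of the matter. The unequal collection is set by the protocol itself, and no analysis plan can recover usual-care events that were never recorded or separate sources that were never flagged. Nor do the other points give usual care a matching route into the study record.

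**Conclusion.** The point holds in conditional form. If the arms are compared on all recorded events, the comparison is open to detection bias, with over-recording in VDOT the likelier direction. Under the stated assumptions the apparent risk ratio runs from 1.00 with equal capture to about 1.13, 1.29 or 1.80 as usual-care capture falls to 80%, 70% or 50% against 90%. None of these capture rates, and none of the true risks used, comes from the document.

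A reader might go further and call the safety comparison biased for certain, or uninterpretable. The document does not support that, since a common side-effect topic exists and the capture gap is unknown. A reader might also infer that a real excess of toxicity under VDOT would be hidden; the more frequent reporting route in that arm points the other way.

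These are listed among the other outcomes. The primary adherence outcome and the sample size are untouched. The change is worth making but is not critical.

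**What to change.** 1. Record the source of each adverse event (follow-up questionnaire, video, phone call, clinic or spontaneous report). If the case report form already does this, nothing needs adding.
2. State that the between-arm comparison of side effects and adverse events rests on the side-effect items asked at months 2, 4 and 6.
3. Word those items identically in the separate usual-care and VDOT follow-up questionnaires. The questionnaires are not shown, so check whether they already match.
4. List video- and phone-reported events separately as descriptive data for VDOT only, and keep every event from every source in safety reporting.

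The cost is one field on the adverse event record, a check of two questionnaires and a sentence in the analysis plan. No safety information is lost. The downsides are that fewer VDOT events enter the comparison, that events which patients do not regard as side effects may fall outside it, and that some difference in recall may remain, since VDOT patients who report daily may remember more at the visit.
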